**1.12 Withdrawal from the Study.**

In accordance with the current revision of the Declaration of Helsinki and applicable regulations, a

patient has the right to withdraw from the study at any time for any reason without prejudice to

his/her future medical care by the physician or at the institution.

Patients may be excluded from study in case of:

-significant protocol violation or non-compliance

-refusal of the patient to continue treatment and observations; withdrawal of consent

-if the investigator believes that for safety reasons (e.g., adverse events), it is in the best interest of the subject to stop treatment.

-if the patient due to renal failure is unable to receive zoledronic acid in two consecutive months (infusion can be delayed for up to three months). In case of tooth extraction, a delay of up to four months is allowed.

-if the patient due to BON stops treatment with zoledronic acid.

-if patients in the control arm experience progressive bone disease and the treating physician find it in the best interest of the patient to reinitiate treatment with zoledronic acid.

-if the subject becomes pregnant

-death

Patients excluded from the study will be followed for 30 days by the local hospital to insure registration of late occurring AE, SAE, SAR and SUSARs

The date and the reason for withdrawal status should be stated in the case report form. If the patient withdraws his or / her consent no further investigations will be conducted. If the patient is excluded for other reasons and it poses no risk for the patient fasting serum bone marker should be measured upon withdrawal, and bone imaging should be conducted no less than one month after withdrawal from the study. Data collected from the patient up until the time of withdrawal will if possible be used in the final evaluation of the study result unless the patient states it otherwise.

As stated in section 1.13, 286 patients need to be randomised to achieve enough power in the study. Patients will be included until this number is reached

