**1.13 Statistical Considerations.**

Primary endpoint:

There are no published data on the incidence on PBD from year 2 and onward in MM. However, there are data showing the annual incidence of the more strict sPBD is approximately 5% in patients receiving continuous zoledronic acid [[31](#_ENREF_31)]. Since we in this study use a less strict definition of progression in bone disease, we assume the annual incidence will be 7.5% instead of only 5% in patients receiving zoledronic acid. Based on data from the MRC IX trial and from an ASH publication in 2012 we expect to see risk reduction rate of 0.5 [[32](#_ENREF_32)]. With a significance threshold of 0.05, one-sided, a power of 80, and a fixed study duration of 2 years, we need a sample size of 143 per group to detect a difference in the primary endpoint. 286 patients in total need to be allocated to the two treatment arms. However, due to the nature of the disease, 30% of all patients will be dead before year two. Due to the in- and exclusion criteria we presume that only 20% of the study population will be dead before stratification. Thus 358 patients in total need to be included in the protocol. Data will be analysed according to the treatment the patients actually received using the Kaplan-Meier analysis. Patients will be analysed per protocol. New data have shown significant reduction in PBD after 4 years treatment with zoledronic acid compared to 2 years of treatment in 170 randomised patients^33^.

Other endpoints:

Serum samples will be collected and stored from all patients. From the calculations above, we expect 32 cases of PBD during year two to four. Bone markers will be measured on these patients from the time of PBD and 6 month prior to the bone event. An equal number of controls will be selected as the number of cases PBD actually observed and bone markers will be measured likewise in these patients. The controls will be selected according the stratification criteria’s (previous autologous stem cell treatment, presence or absence of bone disease at diagnosis, and previous treatment with bortezomib). If multiple options are present the same gender will be chosen, and after that the closest age related. Data will be analyzed as a case control study

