**1.15 Privacy of Personal Data and Data Handling**

Each patient will be assigned a personal identification number on inclusion. The data will be archived in accordance with GCP rules for 5 years in Denmark and Norway and for 10 years in Sweden following completion of the study. The collection and processing of personal data from patients enrolled in this study will be limited to

those data that are necessary to investigate the efficacy, safety, quality, and utility of the study drugs

used in this study.

The data will be recorded on case report forms (CRF). Patients will receive a protocol number for the CRF. A patient log which may pair the protocol number with the civic registration numbers will be kept under lock and key at the sponsor’s research facility. Since this is not a blinded study decoding of the patients will probably not be necessary. However if a situation arises where it is deemed in the best interest of the patient to break to code, this will have to be decided by the national investigator or the sponsor.

Bone markers will not be measured locally. Instead serum samples collected during the study will be stored locally and then later sent to The Haematological Research Unit in Odense, Denmark. Bone markers measured bi-annually will be analysed for all patients. As stated in section 1.13 32 cases and 32 controls will be selected and monthly bone markers will be analysed 6 months retrospectively in these patients. The serum samples are collected for this specific purpose and no in order to created a research biobank. For further details on the bone markers see appendix 2.

Radiological data will be mailed to The Haematological Research Unit in Odense, Denmark. They will be kept there for later review, as specified in appendix 3.

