**1.20 Timescale**

Initiation is expected to occur end 2014, and due to new data inclusion will end 01.12.2020 with a follow up two years the expected termination date is 01.12.2022.

An interim analysis will be conducted at the end in inclusion. The steering committee will then decide if the positive effect of a decrease in the number of PBD outweighs a negative effect of an increased risk of BON, or if the study should be terminated.

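### The 32 PBD cases expected over years 2 to 4 are one year's count (the protocol's own assumptions give about 57), and two rules for ending accrual stand unreconciled.

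*Protocol*

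**What the plan says.** **Planning assumptions (Protocol 1.13).** For the primary endpoint, "we assume the annual incidence will be 7.5% instead of only 5% in patients receiving zoledronic acid", and "we expect to see risk reduction rate of 0.5". The calculation is made "With a significance threshold of 0.05, one-sided, a power of 80, and a fixed study duration of 2 years", and concludes "we need a sample size of 143 per group to detect a difference in the primary endpoint". That is 286 randomised, raised to 358 included to allow for 20% dying before randomisation.

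**Expected cases (1.13, other endpoints).** "From the calculations above, we expect 32 cases of PBD during year two to four". Bone markers are to be measured in these patients and in controls equal in number to the PBD cases that are really seen.

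**Laboratory plan (1.15).** "As stated in section 1.13 32 cases and 32 controls will be selected". Here the number is fixed.

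**End of accrual.** Section 1.12 recalls the 286 needed for power and adds: "Patients will be included until this number is reached". Section 1.20 says "due to new data inclusion will end 01.12.2020 with a follow up two years the expected termination date is 01.12.2022". No total or power is given for the case where the date arrives before the 286th randomisation.

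**The concern.** The 32 is presented as following from the sample-size calculation and as covering two years, but it matches one year of events. A reader who takes it at face value would think the trial expects far fewer events than its power requires. The marker sub-study, which is to yield cut-off values and predictive values, would be planned and budgeted for little more than half the cases the protocol's own assumptions predict.

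The accrual rules raise a different problem. The 80% power belongs to 286 patients with a full two years of follow-up each. If inclusion stops on a date, neither the number nor the follow-up is assured. The protocol does not say which rule governs.

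**Working it through.** **Inputs, all from 1.13:** 7.5% per year on continued treatment; effect 0.5, read as a hazard ratio of 0.5, so 15% per year after stopping; one-sided 0.05 (z = 1.645); power 80% (z = 0.842); two years; 143 per arm.

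**Step 1: reproduce the sample size.**
- Two-year risks with exponential hazards: 1 − exp(−0.15) = 0.139 and 1 − exp(−0.30) = 0.259; sum 0.3985.
- Freedman: events = ((1 + 0.5)/(1 − 0.5))² × (1.645 + 0.842)² = 55.7, so 56; 56/0.3985 = 141 per arm.
- Exponential-rate (Lachin) formula: 139 to 140 per arm.
- Schoenfeld: events = 4 × (1.645 + 0.842)²/(ln 2)² = 51.5, so 52; 52/0.3985 = 131 per arm.
- Inflation: 286/0.8 = 357.5, so 358.

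The stated 143 lies within 3% of the first two formulas, and 358 is exact. The sample size stands.

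**Step 2: reproduce the 32.** 143 × (0.075 + 0.15) = 32.2. This uses annual rates once, so it is one year of events.

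**Step 3: the two-year count with 143 per arm.**

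| Assumption | Expected PBD cases |
|---|---|
| Exponential hazards, no losses | 143 × 0.3985 = 57 |
| Compounded annual risks, no losses | 143 × (0.1444 + 0.2775) = 60 |
| Linear risks, no losses | 143 × (0.15 + 0.30) = 64 |
| Exponential, assumed losses 0.10 per year | 52 |
| Exponential, assumed losses 0.15 per year | 50 |
| Exponential, assumed losses 0.30 per year | 43 |

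The rows with losses use, for each arm with event hazard λ and loss hazard c, the risk λ/(λ + c) × (1 − exp(−2(λ + c))). The loss rates are my assumptions; the protocol states none after randomisation. Even the heaviest does not bring the count down to 32.

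**Step 4: events and power.** Power is Φ(ln 2 × √(d/4) − 1.645) by Schoenfeld and Φ(√d/3 − 1.645) by Freedman.

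| Events d | Schoenfeld | Freedman |
|---|---|---|
| 32 | 62% | 60% |
| 52 | 80% | 78% |
| 57 | 83% | 81% |

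**Step 5: can 32 be right for two years?** Only if 7.5% per year were the rate after stopping: 143 × 2 × (0.0375 + 0.075) = 32.2. Section 1.13 gives 7.5% to patients on zoledronic acid, and that reading would need roughly 220 to 260 per arm, not 143.

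**Step 6: the accrual dates.** A newly diagnosed patient is randomised at year 2 and followed to year 4 (1.7). Four years back from 01.12.2022 is 01.12.2018. Anyone entering by that route later cannot reach year 4 by the end date, apart from the one-month imaging window. A patient entering under the amendment is randomised at inclusion (1.4, 1.6, 1.7) and needs only two years, so inclusion up to 01.12.2020 fits.

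**Step 7: power below 286, for illustration.** The totals are assumed, with no losses and two full years; events = N/2 × 0.3985.

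| Randomised | Events | Schoenfeld | Freedman |
|---|---|---|---|
| 170 | 34 | 65% | 62% |
| 200 | 40 | 71% | 68% |
| 240 | 48 | 77% | 75% |

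**The case against.** **The 32 does little damage.** It appears after the sample size is settled, under the other endpoints, and nothing in the power derives from it. Section 1.13 also ties the controls to the cases observed, so only 1.15 hard-codes the number. This stands: the consequence is a wrong expectation and a wrong laboratory workload in a secondary, partly exploratory study.

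**A reader might infer that the trial has only about 62% power.** The documents do not support that. Their inputs return 139 to 141 per arm against 143, so the error can be placed in the 32.

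**A reader might also infer that the 32 misdirects the interim analysis.** It does not. Section 1.9 sets the interim when half the patients have completed, and 1.20 at the end of inclusion. Neither counts events.

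**A flat 57 would be too precise.** It assumes no death or withdrawal after randomisation, whereas 1.9 expects many deaths during the study and 1.12 lists several grounds for exclusion. This stands, and a range is needed. Nor should 52 be given alone: it is the Schoenfeld figure, while Freedman, which comes closer to 143, needs 56.

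**The dates in 1.20 work for amendment patients.** This stands too. A reader might infer that a third of patients lose follow-up: inclusion from end 2014 to end 2020 is six years, and the last two of the six are affected. With 286 randomised that would mean a mean follow-up of 1.67 years, about 48 events and 77% power (Schoenfeld). It holds only if every patient enters by the original route at a uniform rate, and the documents give no mix of routes. Nor do they say that the date has replaced the 286. Both statements are current text.

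**Conclusion.** The point holds in two separate parts.

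1. The 32 is wrong as labelled. It is one year's count. Two years give about 57 cases on exponential hazards without losses, with a range of about 50 to 64 across the risk models and assumed losses of up to 0.15 per year. This rests on reading the effect as a hazard ratio of 0.5 favouring continued treatment, the reading under which 143 reproduces. The sample size and the 80% power are sound as calculated, though the margin is thin: 57 expected against 52 to 56 needed, and losses of 0.10 to 0.15 per year would use it up. This part is a correction to a planning figure and a secondary sub-study, not a defect in the primary comparison.

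2. Sections 1.12 and 1.20 give two end-of-accrual rules, and no power is stated for fewer than 286. How much power is at stake depends on the number randomised by the date and on the mix of entry routes, neither of which the protocol gives. The illustrative totals show the order of size: about 65% at 170 and 77% at 240 by Schoenfeld, slightly lower by Freedman.

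**What to change.** **Section 1.13.** Replace 32 with about 57 expected PBD cases over years 2 to 4, give the range 50 to 64 with the assumed loss rate behind it, and state that 80% power needs about 52 (Schoenfeld) to 56 (Freedman) events, naming the formula used for 143.

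**Section 1.15.** Replace the fixed 32 plus 32 with all observed PBD cases and an equal number of controls, as 1.13 already provides.

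**Sections 1.12 and 1.20.** Keep one accrual rule. If it is the number, drop or move the closing date. If it is the date, define it as last randomisation by 01.12.2020 with two-year follow-up for everyone randomised, and restate the power for the number actually randomised.

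**Cost.** Wording and restated figures, plus assays for about 20 to 25 more case-control pairs (52 − 32 = 20; 57 − 32 = 25). The sample-size calculation need not change.

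### Section 1.13's expected 32 PBD cases in years two to four is a one-year count; the same inputs give about 57 to 64 over two years, and section 1.15 carries 32 forward as a fixed case number

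*Protocol*

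**What the plan says.** Section 1.13 of the protocol (Primary endpoint) sets the design inputs. For the event rate, "we assume the annual incidence will be 7.5% instead of only 5% in patients receiving zoledronic acid". For the effect, "we expect to see risk reduction rate of 0.5". The error rates and follow-up are given as "With a significance threshold of 0.05, one-sided, a power of 80, and a fixed study duration of 2 years". The result is that "we need a sample size of 143 per group to detect a difference in the primary endpoint", and so "286 patients in total need to be allocated to the two treatment arms".

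Under Other endpoints, the same section turns to the bone-marker case-control analysis: "From the calculations above, we expect 32 cases of PBD during year two to four". On controls it says: "An equal number of controls will be selected as the number of cases PBD actually observed".

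Section 1.15 (Privacy of Personal Data and Data Handling) restates this as a number: "As stated in section 1.13 32 cases and 32 controls will be selected".

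**The concern.** The 32 is presented as a product of the sample-size calculation, and that calculation runs over two years. Yet 32 is what the inputs yield in one year. It is also well below the number of events that 80% power needs at this effect size, so 32 events and 80% power cannot both come from one set of assumptions.

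Two things are at stake. First, this is the only expected event count in the protocol, so anyone using it to judge whether PBD is accruing as assumed has a yardstick about half the right size. Second, it sizes the analysis behind a secondary endpoint, the prediction of PBD from monthly bone markers. Section 1.15 writes it as a fixed number of cases, with no rule for choosing 32 if more occur. Section 1.13 uses all of them.

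**Working it through.** **Inputs (section 1.13).** 143 per group; 7.5% per year on zoledronic acid; ratio 0.5; one-sided 0.05; 80% power; two years. The rate after stopping is not stated. Dividing 7.5% by 0.5 gives about 15% per year, and the check of 143 below supports that reading. The 20% mortality in section 1.13 falls before randomisation and does not reduce the 286.

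**1. Reproducing 32.**
143 × 0.075 = 10.7 and 143 × 0.15 = 21.5; the sum is 32.2. This is one year.

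**2. The two-year count, before losses.**

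| Convention | Calculation | Cases |
|---|---|---|
| Constant hazards 0.075 and 0.15 | 143 × [(1 − e^−0.15) + (1 − e^−0.30)] | 57.0 |
| 7.5% compounded, hazard ratio exactly 0.5 | 143 × [(1 − 0.925²) + (1 − 0.925⁴)] | 59.0 |
| 7.5% and 15% compounded | 143 × [(1 − 0.925²) + (1 − 0.85²)] | 60.3 |
| Simple doubling | 143 × (0.15 + 0.30) | 64.3 |

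**3. Events needed for 80% power** (hazard ratio 0.5, one-sided 0.05; z values 1.645 and 0.842).
- Schoenfeld: 4 × (1.645 + 0.842)² / (ln 2)² = 51.5, so 52.
- Freedman: (1.645 + 0.842)² × (1.5/0.5)² = 55.6, so 56.

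**4. Does 143 rest on two years of events?** With hazards 0.075 and 0.15, the two-year risks are 0.1393 and 0.2592, which sum to 0.3985. Freedman gives 55.6 / 0.3985 = 139.6, so 140 per group, within 3% of 143. Inclusion follows as 286 / 0.80 = 357.5, so 358. The sample size therefore uses two years and the case count uses one.

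**5. Power if 32 were the true two-year count.**
- Schoenfeld: Φ(√(32/4) × 0.693 − 1.645) = Φ(0.316) = 62%.
- Freedman: Φ(√32 / 3 − 1.645) = Φ(0.241) = 60%.

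**6. Can another reading give 32 over two years?**
- *Two-year risks of 7.5% and 15%*, that is, 3.75% and 7.5% per year. The count is then 143 × 0.225 = 32.2. But section 1.13 calls 7.5% annual and assigns it to patients on treatment. This reading would also need 51.5 / 0.225 = 229 (Schoenfeld) or 55.6 / 0.225 = 248 (Freedman) per group, not 143.
- *Attrition in years two to four.* The sample-size text states no rate, so this is an assumption. With a loss hazard d in both arms, expected cases are the sum over λ = 0.075 and 0.15 of 143 × λ/(λ + d) × (1 − e^−2(λ+d)). For d = 0.05, 0.10, 0.20 and 0.30 per year this gives 54.3, 51.9, 47.4 and 43.4 cases. Reaching 32 needs d of about 0.68 per year, which means about 74% lost over two years.

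**The case against.** The strongest reply is that the 32 is an output and nothing in the primary analysis depends on it. This stands. The figures 143, 286, 358 and 80% all follow from the inputs without it. Section 1.12 ties recruitment to 286 randomised patients, not to events. The interim looks are timed by half the patients completing (section 1.9) or by the end of inclusion (section 1.20). No rule in the protocol acts on a total event count. A reader might infer from 32 that the trial is really powered at about 60%. The documents do not support that: their own inputs show that the sample size is sound and the case count is the slip.

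The second reply is that section 1.15 is a data-handling section that explicitly defers to 1.13, and that 1.13 calls 32 an expectation and supplies the working rule. Serum is stored from all patients, so no sample is lost. This largely stands too. A reader might infer that about half the cases will be discarded, but that would mean applying 1.15 against the section it cites. What remains is that 1.15 says a fixed number will be selected, and that the number is wrong in both places.

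Third, section 1.3 describes the bone-marker work as partly explorative. That lowers the stakes but does not make the figure right.

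**Conclusion.** The arithmetic error is real and confined to the expected case count. On the protocol's stated inputs, about 57 to 64 PBD cases are expected between year two and year four before losses, not 32. The range reflects only how an annual rate is carried over two years. It assumes that the ratio of 0.5 means about 15% per year after stopping, which the sample size of 143 supports. No stated attrition and no consistent alternative reading brings the count down to 32.

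The sample size stands. The 60 to 62% power at 32 events shows that 32 and 80% are incompatible; it is not an estimate of this trial's power. The protocol gives no loss rate for years two to four, so any count adjusted for losses is an assumption.

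This should be fixed. It affects the planning and size of the bone-marker secondary endpoint and the protocol's only stated expected event count, and sections 1.13 and 1.15 need to agree.

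**What to change.** In section 1.13, replace 32 with about 57 to 64 expected cases before losses, naming the convention used. Alternatively, state the rates or the attrition for years two to four that lie behind a lower figure, and recheck the 80% power against the 52 to 56 events required. Label any loss-adjusted count as an assumption and give a range; for example, a loss hazard of 0.05 to 0.30 per year gives about 54 down to 43 cases.

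In section 1.15, replace the fixed 32 cases and 32 controls with all observed PBD cases and an equal number of controls, as section 1.13 already provides.

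The change is to text only; recruitment, visits and sample collection are unaffected. The cost is laboratory work: monthly marker assays for about 114 to 128 patients (2 × 57 to 2 × 64) instead of the 64 that section 1.15 foresees, so up to about twice as many. The samples are already planned to be stored.

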In 2003 it was first suggested that treatment with bisphosphonates could cause bisphosphonate induced osteonecrosis of the jaw (BON) [[9](#_ENREF_9)]. BON is a serious disorder where the bone, usually of the mandible, starts to dissolve. The incidence in BON increases with the duration of bisphosphonate treatment and the potency of the bisphosphonate; and is commonly observed subsequently to tooth extraction [[10](#_ENREF_10), [11](#_ENREF_11)]. Because of BON, various recommendations regarding preventive initiatives have been published on how to reduce the incidence of this side effect. These preventive initiatives include; high-risk dental conditions should be treated prior to bisphosphonate initiation, good oral hygiene should be maintained throughout the treatment period, after treatment initiation invasive dental procedures should be avoided if possible, prophylactic antibiotics should be given in case of invasive dental procedures, and the duration of bisphosphonate treatment should if possible be limited [[2](#_ENREF_2), [12](#_ENREF_12)]. In combination, these preventive initiatives have reduced the incidence of BON [[13](#_ENREF_13), [14](#_ENREF_14)]. Concerning the duration of bisphosphonate treatment, most guidelines suggests two years of treatment after which further treatment should be at the discretion of the treating physician [[2](#_ENREF_2), [15](#_ENREF_15)]. The reason for the two years separation is based on very little scientific evidence. But, the two initial bisphosphonate studied had a follow-up of 21 and 24 months respectively [[5](#_ENREF_5), [7](#_ENREF_7)]. There are scarce data concerning what happens once bisphosphonate is discontinued in MM. However we do know that biochemical markers of bone resorption start to increase shortly after discontinuation, and that the rate of the increase is greater if the preceding treatment duration is short [[16](#_ENREF_16)]. Likewise there are data indicating that early re-initiation of bisphosphonate may prevent development of progressive bone disease (PBD) [[17](#_ENREF_17)]. These data could suggest that, by withholding bisphosphonate in order to avoid BON, the patient is subjected to an increased risk of bone pain, hypercalcaemia, or fractures. This schism is becoming increasingly relevant as the expected life time of the patients is increasing these years, thus resulting in a prolonged time period where the patient perhaps receives inferior treatment due to fear of potential side effects.

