
Bone markers in multiple myeloma.

Throughout life, bone is continuously being remodelled with removal of old bone by the osteoclast followed by replacement with new bone by the osteoblast. In MM, bone resorption is generally increased both in regard to numbers and activity of the osteoclast. Bone formation on the other hand follows a more biphasic pattern, being compensatory increased early in the disease, but later as the disease progresses it becomes depressed [[18](#_ENREF_18), [19](#_ENREF_19)]. This imbalance ultimately leads to loss of bone mass and osteolysis. Biochemical markers of bone remodelling are components that are released to the blood during the bone remodelling process. Unlike bone imaging, which provides static data, bone markers provide dynamic information on the current bone turn over rate [[20](#_ENREF_20)]. Furthermore, bone markers can be measured in a blood sample, hopefully negating the need for radiation. Bone markers can be divided into markers of bone resorption and markers of bone formation, thus evaluating each part individually. Recently we have demonstrated that changes in the levels of different bone markers preceded progressive bone disease (PBD) in the individual patient [[21](#_ENREF_21)]. We therefore hypothesis that, in the future, development in bone marker levels in the individual patient can be used to tailor bisphosphonate treatment in the individual patients, as opposed to treatment for a fixed time period in all patients. Our hope is that treatment could be initiated as soon as bone turnover becomes abnormal instead of waiting for painful osteolysis to develop. Likewise, treatment could be withheld when bone remodelling becomes stable thereby avoiding unnecessary side effects. In this study, we want to collect markers of bone resorption and bone formation and thus retrospectively be able to calculate cut of values for the different markers where the best positive- and negative predictive values are achieved. Since this parameter is partly explorative it will the needed afterwards to design prospective trials where we test the clinical usefulness of bone marker guided treatment. Another way to separate the markers is into extracellular components released during the actual bone remodelling process or into cellular components reflecting the number of osteoclasts or osteoblasts respectively. The extracellular markers profit from being highly specific but are also subject to high variation, whereas the cellular markers are less specific but more stable. We also want to use this study to investigate if it is the more specific markers of actual bone remodelling or the more stable cellular markers that are the safest to use in a future prospective clinical trial. The following bone markers will be measured: C-terminal cross-linked Telopeptide of type I Collagen (CTX-I), a bone degradation marker reflecting actual collagen breakdown. Tartrate Resistant Acid Phosphatase isotype 5b (TRAP5b), a bone degradation marker reflecting the number of osteoclasts. Procollagen type I N-terminal propeptide (PINP), a bone formation marker reflecting collagen synthesis. Bone specific Alkaline Phosphatase (bALP) a bone formation marker reflecting the number of osteoblasts, and C-terminal cross-linked Telopeptide of type I Collagen generated by MMPs (ICTP), a bone degradation marker reflecting matrixmetalloproteinase-induced collagen breakdown. ICTP will be measured only at diagnosis. For further details on when bone markers will be measured, please see section 1.7 and appendix 1.

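### Controls for the bone-marker case-control study are chosen without regard to randomised arm or event date, and a 1:1 sample cannot directly give the predictive values the protocol aims for

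*Protocol*

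**What the plan says.** Section 1.13 of the protocol (Other endpoints) expects 32 PBD cases in years two to four. Markers are to be measured in each case from the time of PBD and over the six months before it. For controls: "An equal number of controls will be selected as the number of cases PBD actually observed and bone markers will be measured likewise". The selection factors are the three randomisation strata (prior autologous transplant, bone disease at diagnosis, prior bortezomib), with tie-breakers: "If multiple options are present the same gender will be chosen, and after that the closest age related". Randomised arm and time since randomisation are not among them. The analysis is described only as that of a case-control study.

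Section 1.3 gives the purpose, which is to "calculate cut of values for the different markers where the best positive- and negative predictive values are achieved". It calls this part partly explorative and says prospective trials must follow. Section 1.3 also states that "biochemical markers of bone resorption start to increase shortly after discontinuation". The corresponding secondary endpoint in section 1.5 asks whether monthly marker values predict PBD from year 2 to year 4. Section 1.15 adds that half-yearly markers are analysed in everyone, but monthly markers only in the 32 cases and 32 controls.

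**The concern.** On the protocol's own premises, stopping zoledronic acid raises resorption markers and also raises the risk of PBD. If controls are drawn without regard to arm, the cases contain more patients off drug than the controls do. A marker could then separate the two groups merely because it shows who has stopped. The treating physician already knows that, so a marker useful for tailoring treatment has to predict PBD among patients with the same treatment status.

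Timing raises a related problem. A control has no PBD date, and the rule does not say which six months of the control's samples are used. Marker levels change with time since stopping, so unaligned windows add a second difference between cases and controls.

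The third issue is the criterion for cut-offs. Positive and negative predictive values depend on how common PBD is, and a 1:1 sample fixes that at one half by design. What is at stake is which marker and which cut-off go forward to the prospective trial.

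**Working it through.** **Inputs, all from section 1.13 unless noted.** On drug, "we assume the annual incidence will be 7.5% instead of only 5% in patients receiving zoledronic acid". Effect: "we expect to see risk reduction rate of 0.5". I read this as a hazard ratio of 0.5, which gives 15% per year off drug; the 15% is derived, not stated. Design: "With a significance threshold of 0.05, one-sided, a power of 80, and a fixed study duration of 2 years". The stated size is 143 patients in each arm. Allocation is 1:1 (section 1.7).

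**The plan's own figures.** With hazards of 0.15 (arm A, stopped) and 0.075 (arm B, continued) over 2 years:
- pA = 1 − exp(−0.30) = 0.259; pB = 1 − exp(−0.15) = 0.139.
- n per arm = (1.645 + 0.842)² × (1/0.259 + 1/0.139) / (ln 2)² = 142, against the stated 143. The reading of the rates is therefore sound.
- Expected cases over 2 years: 143 × (0.259 + 0.139) = 57. The stated 32 equals 143 × (0.075 + 0.15) = 32.2, a one-year count. I carry both counts below.

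**Arm mix, 2-year risks.**

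| | Arm A (off drug) | Arm B (on drug) | Share off drug |
|---|---|---|---|
| Cases | 37.1 | 19.9 | 65.0% |
| Non-cases | 105.9 | 123.1 | 46.3% |

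Odds ratio = (37.1/19.9) / (105.9/123.1) = 2.16. One-year risks give 66.7% against 47.9%, odds ratio 2.18. Matching on the three strata does not help: randomisation is stratified on the same factors, so they carry no information about arm.

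**Effect on a marker with no predictive value within arm.** Assumption: the marker is normal with SD 1 in each arm and shifted upward off drug. The protocol gives no shift, so I use a range. Cases and controls were simulated with the arm shares above and compared by a two-sided 5% t-test.

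| Shift off drug | 32 cases + 32 controls | 57 + 57 |
|---|---|---|
| 0.5 SD | about 7% | about 7% |
| 1 SD | about 10% | about 15% |
| 2 SD | about 19% | about 30% |

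With each control taken from the case's arm, the rate returns to about 5%. In discrimination terms the same marker shows an AUC of about 0.55 (1 SD) to 0.58 (2 SD) instead of 0.50.

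**Predictive values.** PPV = se·p / [se·p + (1 − sp)(1 − p)]; NPV = sp(1 − p) / [sp(1 − p) + (1 − se)p]. Sensitivity and specificity are assumed, since the protocol gives none.

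| Prevalence p | PPV, 80/80 | NPV, 80/80 | PPV, 70/70 | NPV, 70/70 |
|---|---|---|---|---|
| 50% (1:1 sample) | 80% | 80% | 70% | 70% |
| 19.9% (57/286) | 50% | 94% | 37% | 90% |
| 11.2% (32/286) | 34% | 97% | 23% | 95% |

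**The case against.** **Much of this could be settled in an SAP.** The protocol does not say that predictive values will be read from the raw 1:1 sample, and it does not rule out adjusting for arm. The randomised cohort is fully listed and its PBD incidence will be known, so correct values remain obtainable. This stands. A reader might infer that the PPV and NPV will be wrong; the document supports only that they would be wrong if read directly. What an SAP cannot do without contradicting section 1.13 is change the selection rule, which is fixed there.

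**Not every marker is covered.** A reader might also infer that arm distorts every marker association. Section 1.3 speaks only of resorption markers and says the rise is greater after short prior treatment, whereas here it has lasted about two years. Nothing is said about how stopping affects the formation markers PINP and bALP. The claim is therefore firm for CTX-I and TRAP5b and only possible for the others.

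**Arm may act through the marker.** If stopping raises resorption and resorption leads to PBD, matching on arm removes a real part of the signal. This is true, and it is a cost of the fix. The between-arm comparison of all four markers, already a secondary endpoint in section 1.5, covers that part.

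**Timing and checks.** Measuring controls likewise may be meant as the case's window, and a settled level shift cancels from within-patient change. However, the window is not stated and the shift need not have settled. Half-yearly markers in all patients would help reveal a marker that merely tracks treatment, but on a coarser schedule than the monthly values the endpoint concerns.

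**Conclusion.** The point holds for the study as section 1.13 specifies it. The selection rule is complete, and it leaves out a factor that the protocol itself links to both resorption markers and PBD. The arm imbalance (65% against 46% off drug, odds ratio about 2.2) follows from the protocol's rates once 0.5 is read as a hazard ratio.

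The consequence for association tests is moderate. False-positive rates of about 10–19% (32 cases) or 15–30% (57 cases) rest on assumed shifts of 1 to 2 SD and on no later adjustment for arm; at 0.5 SD the excess is small. The predictive-value discrepancy is larger (80% against 34–50% for an assumed 80/80 marker) but arises only if values are taken straight from the 1:1 sample.

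This is a secondary, partly explorative endpoint, and the primary comparison is untouched. It should still be corrected before controls are selected, because the choice of controls is harder to repair afterwards.

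**What to change.** In section 1.13:

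1. Select each control from patients in the same randomised arm who are still free of PBD at the same time since randomisation as the case's event, and measure the control over the same six-month window. Apply the existing factors (three strata, then gender, then age) after that.
2. Analyse the matched sets by conditional logistic regression. If arm is not matched, state that the analysis will be stratified by arm or adjusted for it.
3. State that PPV and NPV will be computed at the cohort incidence of PBD, or with inverse sampling weights that follow the matched selection. A flat factor is only an average: 254/32 = 7.9 with 32 cases.

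Cost: wording only. Serum is stored from all patients and assayed later, so the number of visits and assays does not change. Gender and age matching becomes looser, and within-arm matching gives up the part of the marker signal that comes from stopping the drug.
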